## Abstract

**Background:**

After residential care placement, family members may be exposed to stressors like difficulty in role changes, interpersonal conflict with facility staff, and emotional torment. These can threaten family members’ own health and well-being and even influence the extent they involve in their relative’s care. This study aims to evaluate an online education intervention for Chinese family members whose relatives with dementia have been placed into a residential care facility.

**Methods:**

This protocol describes a two-arm randomised controlled trial. A total of 150 family members of residents with dementia will be recruited from four to six residential care facilities in Xi’an, Shaanxi, China and randomly allocated to either the intervention or control group. Family members in the intervention group will receive a six-week group-based online education intervention, while those in the control group will receive routine care. Family members’ stress, coping, caregiving burden, and family involvement, as well as their relative’s behavioural and psychological symptoms of dementia will be assessed at immediately post-intervention and six-week follow-up. Effectiveness of the intervention will be analysed by generalised estimating equation model, based on the intention-to-treat principle. A process evaluation of the intervention will also be undertaken.

**Discussion:**

This study will be of great significance in addressing family members’ stressors after institutionalising a relative with dementia and promoting the implementation of family-centred care in practice especially in residential care facilities.

**Trial registration:**

Chinese Clinical Trial Registry, ChiCTR1900024582, Registered 18 July 2019.

## Background

Previous studies have found that when family caregiving cannot satisfy the care needs of a relative with dementia, family members may choose to place him/her into a residential care facility [1–3]. Alzheimer’s Association has recently revealed that 42% of residents in residential care facilities and 48% of nursing home residents have Alzheimer’s or other dementias [4]. Residential care transition in fact is a stressful experience not only for persons with dementia but also for their family members. For persons with dementia, admission to a residential care facility indicates loss of their familiar surroundings and people [5], and thus may result in a worsening of behavioural and psychological symptoms of dementia (BPSD) [6]. For family members, residential care placement can to some extent reduce their direct care obligations [7, 8]; yet, it does not represent end of the caregiving process and family members’ stress will never be completely eliminated [9, 10]. Guilt, feeling of loss, and feeling of failure have been reported in family members after residential care placement [6, 9–13]. Schulz et al. [12] even found that family members who have institutionalised a relative with dementia experienced as a high level of depressive symptoms and anxiety as that while they provided in-home caregiving.

The philosophy of family-centred care emphases that families are essential allies for quality and safety of health care [14], and health care professionals should dedicate efforts to maintain family members’ control when providing care services for an individual [15]. Over the past two decades, several interventional studies have been conducted to assist family members to cope with stressful situations after placing a relative with dementia into a residential care facility; however, the duration and focus of the interventions varied with each other [16–21]. The *Family Visit Education Programme* (FVEP) in 1999 can be regarded as a pioneer study in this field [16]. This eight-week group-based education intervention was designed to teach primary family visitors on how to effectively communicate and interact with their relatives with dementia during visiting [16]. McCallion et al. [16] found that the FVEP could significantly reduce primary family visitors’ stress in caregiving and residents’ behavioural symptoms, depression, and irritability. Robison and colleagues [17] have also conducted an education intervention, *Partners in Caregiving* (PIC), for family members of nursing home residents with dementia, but focused on communication and cooperation between family members and facility staff. Results showed that after intervention residents’ behavioural symptoms were significantly reduced in the intervention group when compared with controls. But family members’ perceived hassles with staff and caregiving burden in the intervention group were not significantly different from that of the control group [17]. More recently, Paun et al. [18] designed another education intervention, *Chronic Grief Management Intervention* (CGMI) to deliver family members knowledge of dementia, skills in communication, conflict resolution, and hands-on care in the context of long-term care, and grief management skills. This 12-week group-based intervention also showed beneficial effects, with family members who received the intervention reporting significantly lower lever of grief and guilt than those in the control group [18].

Additionally, one psychoeducation intervention [19] and two psychosocial support interventions were also identified [20, 21]. Underpinned by a perspective of empowerment and the model of stress and coping, the 10-week *Taking Care of Myself* psychoeducation intervention employed group sessions to help daughter caregivers feel at ease with their relatives, express the point of views to health care staff, avoid emotional torment, deal with loss, call upon support network, and take care of themselves [19]. Ducharme et al. [19] found that this intervention was effective in reducing daughter caregivers’ stress appraisal and improving their use of coping strategies. With regard to the two psychosocial support interventions, the *Family Intervention: Telephone Tracking-Nursing Home* (FITT-NH) was a purely telephone-delivered intervention based on the stress and coping model. This three-month intervention aimed to identify and address the acute stressors (e.g. family-staff interaction, satisfaction with the facility, and guilt about the placement decision) of family members who were within two months of placing a relative with dementia into a nursing home through 10 telephone contacts [20]. In contrast, the *Residential Care Transition Module* (RCTM) was a multicomponent intervention including psychoeducation, promotion of communication, problem solving, patient behaviour management strategies, concrete goal planning, knowledge about treatments in the residential care facility, as well as ad hoc counselling [21]. Findings indicated that family members receiving the FITT-NH could significantly reduce their feelings of guilt and hassles with facility staff [20], and family members receiving the RCTM intervention reported significantly reduced levels of role overload and caregiving distress [21].

Although current evidence in this field is limited, it can be seen that providing family members with emotion management skills [18–20], enhancing family members’ competence in communicating and interacting with residents [16, 18, 19, 21], teaching family members skills in building positive relationship with facility staff [19, 21], and/or teaching family members strategies to recognise and cope with new roles and ongoing problems after residential care placement [20, 21] can improve family members’ emotional distress (i.e. guilt, role overload, grief) [18, 20, 21], stress appraisal [19], and stress in caregiving [16, 21]. Additionally, improving family-resident communication and interaction or family-staff partnership is promising for reducing residents’ depression [16] and behavioural symptoms [16, 17]. China has the largest number of population with dementia worldwide, and more than half of nursing home residents are reported to be living with dementia [22]. However, no intervention studies to date are available for Chinese family members of people with dementia in residential care facilities. In order to design an intervention for this population, we have conducted a qualitative study in 17 Chinese family members whose relatives with dementia had been placed into residential care facilities to explore their stressors. Findings showed that Chinese family members experienced multiple stressors after placement. Firstly, Chinese family members were criticised as unfilial by people around and thus experienced a high level of guilt and stress after placement. This is mainly because that in the traditional Chinese culture of filial piety older people are supposed to be cared for by the younger generation at home rather than being placed into a residential care facility [23]. Moreover, the facility fees in China were generally high, which to some extent caused a financial burden for family members. Additionally, continuing caregiving at the residential care facilities has aroused a series of difficulties (e.g. communicating with relative with dementia, addressing behavioural problems, building harmonious relationship with facility staff) that created challenges and frustration for family members. Lastly, suboptimal care provided by the facilities also caused worries for family members. As suggested, people in Asian culture tend to adjust to stress with the aim of creating harmony between self and the environment, instead of removing the stressors or changing features of the environment in order to align with one’s needs [24]. In our qualitative study, we also found that Chinese family members were more likely to accept the reality rather than seeking information to resolve problems when faced with stressors.

With the government’s policy inducement, the number of residential care facilities in China has rapidly increased in recent years but the care quality in residential care facilities indeed are still in the developmental stages [25]. Most caregivers working in residential care facilities have insufficient knowledge and skills about dementia care and thus the care they provide is suboptimal [26, 27]. The expenses of living in a residential care facility are not covered by medical insurance in China [28]. Family members’ stress relating to suboptimal care in the facility and high facility fees may need to be resolved from the government level, such as providing standardized dementia care training for care providers and establishing a robust long-term care insurance system [28, 29]. For other identified stressors, we have designed an online education intervention to facilitate Chinese family members reappraise their situations and to enhance their skills in coping with stressful situations after placement. This study aims to evaluate the effectiveness of the online education intervention. The objectives are: (a) to evaluate whether the intervention can reduce stress and improve coping in Chinese family members compared to routine care; (b) to evaluate whether the intervention can reduce caregiving burden and increase care involvement in Chinese family members compared to routine care; and (c) to evaluate whether the intervention can indirectly reduce residents’ BPSD compared to routine care. We hypothesise that at post-intervention and six-week follow-up, family members in the intervention group will report lower level of stress, higher level of use of coping strategies, lower level of caregiving burden, higher level of involvement in their relative’s care, and residents in the intervention group will have lower level of BPSD, when compared to those in the control group.

### Theoretical underpinnings

This study will be underpinned by the model of stress and coping [30–33]. In this model, stress is a particular relationship between the person and the environment that is appraised by the person as taxing or exceeding his or her resources and endangering his or her well-being [31]. When faced with an event, the person firstly evaluates whether it is irrelevant, benign-positive, or stressful for his or her well-being (primary appraisal) [31]. Once the event is judged as stressful (harm/loss, threat, or challenge), a further form of appraisal becomes salient, that of evaluating what can be done to overcome or prevent harm or to improve prospects for benefit (secondary appraisal) [30, 31]. In appraisal, event uncertainty has a great potential for creating psychological stress [31]. It can be somewhat interpreted as that the more uncertain the person perceives about an event, the more likely he or she appraises it as stressful. Moreover, the extent to which a person believes he or she can handle the person-environment relationship (beliefs about personal control) affects whether and to what extent the person feels stressful in that encounter [31].

Faced with a stressful situation, the person will make efforts to regulate stressful emotions to the problem (emotion-focused coping) and/or manage or alter the troubled person-environment relation causing the stress (problem-focused coping) [33]. In the process of coping, the person’s problem-solving skills and social support can serve as important coping resources [31]. Coping is constantly changing cognitive and behavioural efforts to manage specific demands that are appraised as taxing or exceeding the recourses of the person [31]. If coping results are unfavourable, the person then may change to meaning-focused coping (e.g. benefit finding). Meaning-focused coping is, in its essence, appraisal-based coping in which the person draws on his or her beliefs and existential goals to motivate and sustain coping and well-being during a difficult time [32].

Based on the model of stress and coping, the development of efficacious interventions for reducing a person’s stress should dedicate efforts to cognitive appraisal of the person-environment relationship and available coping resources and use of coping strategies. Interventions to facilitate family members to reappraise the situations (reappraisal/meaning-focused coping), to manage negative emotions (emotion-focused coping), and to deal with stressful situations (problem-focused coping) after residential care placement are anticipated to result in positive outcomes.

## Methods

### Study design

The protocol describes a multicentre, two-arm, assessor-blind randomised controlled trial (RCT), with randomisation of family members of residents with dementia rather than residential care facilities. The CONSORT flow diagram is shown in Fig. 1. Although there might be crossover effects between family members within a residential care facility in which some belong to the intervention group and others to the control group, we still choose an individual RCT design because of its ability to deal with known and unknown confounding factors. To avoid the contamination between participants of the two groups, some strategies will be employed, such as asking participants in the intervention group not to share the intervention information with others.

**Fig. 1 Fig1:**
[figure not shown]
CONSORT flow diagram of the trial

### Participants and recruitment

Family members of residents with dementia will be recruited from four to six medium-sized residential care facilities (100–300 beds) in Xi’an, Shaanxi, China. Posters will be available in the studied facilities to encourage more interested and eligible family members to participate in the trial. Potentially eligible and interested participants will be referred to the researchers by nurses who work in the studied facilities. The researchers will then approach the potentially eligible participants to determine their eligibility and invite them to participate in this trial. Information sheets will be provided to the eligible participants and any questions or inquiries will be answered by the researchers.

To be eligible, the participants should (a) be family members of residential care facility resident who has a medical diagnosis of dementia, (b) be aged 18 years or older, (c) provide the most hours to their relative’s care after placement, (d) have a smartphone and be able to use it, (e) be willing to participate in this study, and (f) be able to read, write and understand Chinese. Exclusion criteria of the participants are: (a) having severe mental disorders (e.g. schizophrenia), (b) having impaired cognitive ability, (c) being a family member whose relative with dementia is at end of life (i.e. the life expectancy is projected to be six months or less), (d) being a paid caregiver, (e) receiving psychotherapies during the period of this study, and (f) participating in other relevant psychosocial interventions or programmes during the period of this study. Participant recruitment for this trial is currently ongoing.

### Sample size estimation

Sample size is estimated based on the primary outcomes, specifically, changes in family members’ stress. In this study, effect size of family members’ stress reduction is anticipated to be medium at 0.50. It is estimated that a sample size of 128 participants (64 per group) will provide this study with 80% power at 5% level of significance (two-tailed). Attrition rates in previous studies ranged from 0% [21] to 34.3% [34], most of which were less than or around 15% [16–18, 20]. In consideration of 15% attrition rate, sample size of this study is finally estimated to be 150 family members (75 per group).

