### Intervention group

Participants in the intervention group will receive a six-session group-based (6 to 10 participants) online education intervention. The intervention will be delivered on a weekly basis, approximately 60 min per week. Participatory approaches (e.g. experience sharing, brainstorm) will be used during the intervention delivery. Participants will be encouraged to complete the whole intervention through text message reminders; yet the situation that participants discontinue the allocated intervention because their relative with dementia dies or moves out of the studied facilities will be allowed.

Session 1 aims to facilitate the participants to reappraise the situations they are facing with, through improving their understanding of dementia. Specifically, the researcher will provide the participants with basic dementia knowledge especially its progression and manifestations at different stages. These kinds of information are anticipated to reduce the participants’ uncertainty about dementia, which may further facilitate the participants to reappraise the situations they are facing with.

Session 2 aims to help the participants manage negative emotions after residential care placement. Firstly, the participants will be encouraged to share their experiences of managing negative emotions after residential care placement. The researcher will introduce the participants some emotion management strategies (e.g. accepting the reality, benefit finding, and humour). In particular, the researcher will guide the participants to find benefits of residential care placement in order to help them reframe stressful situations by wresting positive values form adversity.

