### Data management and analysis

Data will be double entered and checked in EpiData 3.1 (The EpiData Association, Odense, Denmark) and will then be exported to Statistical Package for the Social Sciences (SPSS) version 25.0 (IBM Corporation, Armonk, New York, USA) for analyses. The distribution normality of the continuous variables will be tested by One-Sample Kolmogorov-Smirnov test. The baseline homogeneity between the intervention group and the control group will be tested using the Student’s T test, Mann-Whitney U test, Chi-square test, and Fisher’s exact test, where appropriate. All outcome measures will be compared within and between groups. The generalised estimating equation (GEE) model will be utilised to analyse the intervention effects, with controlling for confounding factors such as the family members’ age, gender, educational attainment, and relationship with the residents, and the residents’ age, gender, educational attainment, type of dementia, and length of stay in the facility. The analyses will be performed based on the intention-to-treat (ITT) principle. For ITT analysis, missing data will be dealt by using the last observation carried forward method, whereby the last available measurement for each participant at the time point prior to withdrawal from the study is retained in the analysis [47]. Statistical significance will be set at *p* < 0.05; all tests will be two-tailed.

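### The 80% power claimed for 64 per group assumes no correlation within the intervention's delivery groups of 6 to 10; power should be restated over an ICC range and delivery group brought into the analysis

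*Protocol article*

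**What the plan says.** Under Sample size estimation, the protocol article bases the sample size on family members' stress: "stress reduction is anticipated to be medium at 0.50". From this it concludes that "a sample size of 128 participants (64 per group) will provide this study with 80% power at 5% level of significance (two-tailed"). The only inflation is for loss to follow-up: "In consideration of 15% attrition rate, sample size of this study is finally estimated to be 150 family members (75 per group"). That section mentions no ICC or design effect.

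Under Intervention group: "Participants in the intervention group will receive a six-session group-based (6 to 10 participants) online education intervention". Sessions are weekly and use participatory methods such as sharing of experience. Under Control group, the comparator is routine care with nothing added, so controls have no delivery groups. Under Study design, individual family members are randomised. That section discusses contamination within a facility but not correlation within delivery groups.

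Under Data management and analysis: "The generalised estimating equation (GEE) model will be utilised to analyse the intervention effects". The named adjustment factors are characteristics of the family member and the resident; delivery group is not among them. The cluster unit and working correlation of the GEE are not stated. Withdrawals are handled by last observation carried forward (LOCF) under intention to treat.

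**The concern.** People who attend six sessions together, share a facilitator and discuss their experiences may end up with correlated stress scores. Here that can happen in one arm only, so the design is partially nested. Variation between delivery groups then adds to the variance of the intervention mean and hence to the variance of the treatment difference. A sample size that leaves no room for it gives less power than stated.

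An analysis that allows for repeated measures within a person, but not for correlation between people in the same group, would also understate the standard error. The false-positive rate on the primary outcome would then exceed 5%. The Discussion says that beneficial results would lead to wider dissemination, so a false positive has practical consequences.

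**Working it through.** **Inputs from the article.** Effect 0.50 SD, two-sided 5%, 64 per arm evaluable, 75 per arm enrolled, 15% attrition, delivery groups of m = 6 to 10 in the intervention arm only.

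**Assumed inputs.** ICC of 0.01, 0.02, 0.05 and 0.10, because the article gives none. Total variance is taken as equal in both arms, and no gain is credited for covariates or repeated measures.

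**1. The plan's own figure.** A two-sample t-test with independent observations, d = 0.50 and 64 per arm, has power 80.1% (79.5% at 63 per arm). So 64 is the smallest size that reaches 80%. For attrition, 128 / 0.85 = 150.6, against the stated 150. The figure reproduces with ICC = 0 and has no slack.

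**2. Number of groups.** 75 / 10 = 7.5 and 75 / 6 = 12.5, so 75 participants form about 8 to 12 groups.

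**3. Formulas for clustering in one arm.**
- Design effect in the intervention arm: DE = 1 + (m − 1) × ICC.
- Standard error of the difference in SD units: SE = √(DE/64 + 1/64).
- Power, normal approximation: Φ(0.50/SE − 1.96).
- Power, small-sample version: noncentral t with Satterthwaite df = (v1 + v2)² / [v1²/(k − 1) + v2²/63], where v1 = DE/64, v2 = 1/64 and k = 64/m groups.
- Type I error if groups are ignored: 2 × [1 − Φ(1.96 / √((1 + DE)/2))].

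**4. Worked case, m = 8 and ICC 0.05.**
- DE = 1 + 7 × 0.05 = 1.35.
- SE = √(2.35/64) = 0.1916, and 0.50/0.1916 = 2.61.
- Power = Φ(2.61 − 1.96) = 74.2%.
- df = (0.02109 + 0.01563)² / (0.02109²/7 + 0.01563²/63) = 20.0, giving power 69.9%.
- Type I error if groups are ignored: 1.96/√1.175 = 1.81, giving 7.1%.

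**5. Full range at 64 per arm, m = 6 to 10.**

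| Assumed ICC | Power, normal approx. | Power, small-sample df | Type I error if groups ignored |
|---|---|---|---|
| 0.01 | 79.0-79.8% | 74.6-77.3% | 5.3-5.5% |
| 0.02 | 77.3-78.8% | 72.5-76.3% | 5.6-6.0% |
| 0.05 | 72.4-76.0% | 66.6-73.1% | 6.5-7.7% |
| 0.10 | 65.1-71.6% | 58.1-68.2% | 8.0-10.4% |

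The normal approximation starts from 80.7% at ICC = 0. The small-sample column also includes the price of estimating variance from few groups. At ICC = 0 and m = 8, DE = 1 and df = 4/(1/7 + 1/63) = 25.2, so power is already 77.6%.

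**6. If all 75 per arm are analysed.** With LOCF, participants who withdraw stay in the analysis. Replacing 64 by 75 at m = 8, power is 84.1%, 80.6% and 75.0% at ICC 0.02, 0.05 and 0.10 (81.4%, 77.3% and 70.9% with small-sample df). These are upper bounds, because carried-forward values may dilute the effect.

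**The case against.** The strongest reply is that everything beyond the sample-size arithmetic rests on what the article does not say.

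- **The analysis.** A reader might infer that the GEE treats all participants as independent and that its standard errors are too small. The article does not support this. It names the GEE and its covariates but not the cluster unit, which a full analysis plan could specify. This objection stands, so the type I error figures are conditional on clustering by person only. It does not affect the power claim, which the article states outright.
- **The ICC.** A reader might also infer that 80% power is certainly not achieved. The article gives no ICC. At 0.01 the loss is about 1 point or less from 80% by the normal approximation, or 3 to 5 points with small-sample df. The loss becomes clearly material from about 0.05, and nothing in the article places the ICC there. This also stands.
- **The number analysed.** With 75 per arm under LOCF, power at groups of 8 remains near 80% at ICC 0.05 by the normal approximation. If 64 is instead the number left after attrition, groups shrink too: 8 × 0.85 = 6.8. At ICC 0.05 that gives DE 1.29 and power 75.3% (71.9% with small-sample df), slightly better than the worked case. Both points are fair and narrow the loss without removing it.
- **Precision from covariates and repeated measures.** Some power may be recovered this way. The sample-size section claims no such gain, and it would not correct the type I error of an analysis that ignored groups.
- **Group membership.** The article does not say that membership is fixed across the six sessions. Shared sessions are enough for correlation to arise, but shifting membership would complicate a single group effect.

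**Conclusion.** The point holds in a conditional form. The 80% claimed for 64 per group is the independent-observations figure and, at that size, is correct only if the within-group ICC is zero. The plan's own delivery in participatory groups gives reason to doubt that.

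The size of the shortfall cannot be fixed from the article. At 64 per arm it is negligible to a few points at ICC 0.01, depending on the method. By the normal approximation it is 4 to 8 points below 80% at 0.05 and 8 to 15 points at 0.10. It is smaller if all 75 per arm contribute undiluted data. An inflated type I error follows only if the GEE is clustered on the person alone, which the article neither states nor rules out. These figures assume clustering in the intervention arm only; a design effect applied to both arms would overstate the loss.

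**What to change.** 1. Record each intervention participant's delivery group now, since the article says recruitment is ongoing and membership may be hard to reconstruct later. Note any change of group.
2. State how the analysis represents delivery group. One option is a partially nested mixed model: a random group effect in the intervention arm only, controls as singletons, repeated measures within person, and Satterthwaite or Kenward-Roger degrees of freedom. The other is a GEE clustered on delivery group, with controls as singletons and a sandwich estimator corrected for the small number of clusters.
3. Replace the flat 80% with power over ICC 0.01 to 0.10, and say whether 64 or 75 per arm are taken as analysed.

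The cost is one recorded variable, a changed model statement and a less favourable stated power. No extra enrolment is needed.
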